### 2.3. Recruitment

Study posters and flyers will be displayed at multiple hematology clinics across Brisbane, Australia. Study co-investigators will directly approach eligible patients with MM. The study will also be advertised via Myeloma Australia and the Leukaemia Foundation support group network for participant self-referral.

Eligible participants will receive the Participant Information Sheet, Participant Consent Form, and Medical Doctor Clearance Form. Their doctor’s written clearance and the signed Participant Consent Form will be collected and securely stored by the principal investigator.

### 2.4. Randomization

Following completion of the baseline testing session, participants will be stratified by disease stage (active treatment, transplant eligible; active treatment, transplant non-eligible; non-active; relapsed) before being randomly assigned (1:1 allocation ratio) to waitlist control (WT) or exercise intervention (EX) group. A research officer independent of the study will perform the randomization using a computerized random number generator. To ensure allocation concealment, a block size of four will be used. Randomization history will be kept secure by the independent research officer in an electronic password-protected file. The allocation result will be communicated in confidence by the independent research officer to the trial’s accredited exercise physiologist (AEP) within 48 h after completing the baseline testing session. The principal investigator will conduct all testing sessions and analyses and be blinded to group allocation. Un-blinding will not be permissible under any circumstances. Due to the nature of the study, neither the AEPs prescribing the training nor participants can be blinded to the randomization assignment.

### 2.5. Exercise Intervention

Participants will complete the modular multi-modal resistance, aerobic, and impact loading exercise program under the supervision of the trial AEP on two days per week, in addition to one home-based session. Supervised exercise sessions will be offered at multiple locations across southeast Queensland, Australia: North Lakes Health Precinct, Greenslopes Private Hospital, Princess Alexandra Hospital, Royal Brisbane and Women’s Hospitals Hospital, and The University of Queensland. A familiarization session with the trial AEP will be completed in the week prior to commencement to explain the exercise program and guide participants through several exercises that are more technically challenging. The 60 min training session will follow the procedure as described in Figure 2. The exercise intervention is designed to provide an optimal stimulus to the cardiorespiratory, skeletal, and neuromuscular systems while maximizing compliance and retention. The program adheres to the American College of Sports Medicine (ACSM) Guidelines for Exercise and Cancer for improving HRQoL [8]. The exercise prescription will be individualized by the trial AEP based on the participants’ goals, exercise history and preferences, baseline testing results, and health status, including location/extent of bone metastases. All participants will be asked to maintain customary physical activity and dietary patterns over the intervention period (apart from the programmed exercise).

Prior to each supervised session, the trial AEP will measure the participants’ heart rate (HR) and blood pressure to identify potential contraindications to commencing exercise, as outlined by the ACSM [40]. Each session will commence with a 5 min warm-up comprising low-impact aerobic activities, such as stationary cycling, at a progressive very light/light intensity (rating of perceived exertion (RPE) of 9–10 on the 6–20 Borg Scale), and conclude with a 5 min cool-down period of stretching activities.

The 20 min aerobic exercise component will comprise 60–85% peak HR (HR_peak_) (equivalent to RPE 12–15; Polar Electro Oy, Kempele, Finland), interspersed with 2 × 4 min bouts of high intensity (>85% HR_peak_; equivalent to RPE 16–19) exercise. HR_peak_ from the baseline cardiopulmonary exercise test (CPET) will be used to calculate the target intensity if the criteria for achieving maximal oxygen uptake (V̇O_2max_) is met. Where the baseline CPET result does not meet the criteria for a V̇O_2max_ result, i.e., peak oxygen uptake (V̇O_2peak_) or an invalid test, HR_peak_ will be determined using the equation [41]:HR_peak_ = 208 − (0.7 × age in years) 

The resistance exercise and impact loading prescriptions will be guided by the protocols for people with bone metastases used by Hart et al. [42] and Rief et al. [43]. Specifically, the resistance training component of the program will include exercises that target the major trunk, upper, and lower body muscle groups, modified based on the location and extent of bone lesions and bone pain [42]. Intensity and volume of resistance exercise will involve 2–3 sets of 6–10 repetition maximums (RMs) (i.e., the maximal weight that can be lifted 6 to 10 times), with 30–60 s rest between sets. Target intensity will be 60–85% (6–9 on the OMNI-Resistance Exercise Scale of Perceived Exertion (OMNI-RES) [44]. To ensure the progressive nature of the training program, participants will be encouraged to work past the specific RMs prescribed. The resistance will be increased by a 5–10% increment for the next set/training session if the participant is able to perform more repetitions than the RMs specified during a set.

Bone loading activities will progressively increase across the intervention from 40 impacts per session to 100 impacts per session for non-affected skeletal sites [45]. Participants with pelvic, axial skeleton (lumbar), or lower limb bone lesions will be prescribed isometric exercise targeting the spine and pelvis in positions of support, e.g., supine, prone, or seated for unstable lesions. For participants without the aforementioned bone lesions, the intensity of impacts, based on the ground reaction forces produced, will be progressively increased across the intervention, i.e., level 1: isometric exercise targeting spine and/or pelvis; 2: marching; 3: stomping; 4: jumping; 5: drop jump from height (range 10–30 cm) [45]. Progression will account for any pre-existing musculoskeletal injuries and/or pain. Participants will be instructed to land on their heels with approximately 5° knee flexion on impact. One minute rest periods will separate jump sets with a minimum of four sets of 20 impacts per set. Unilateral exercises, i.e., marching, stomping, will have a minimum of 80 impacts per leg (4 × 20 impacts per leg), with a minimum of 80 total impacts for bilateral exercises, i.e., jumping, drop from height.

Exercise sessions will be cancelled/postponed if the participant experiences a fever (>38.0 °C), infection, platelet count <50 × 10^9^/L, hemoglobin <90 g/L, higher grade cardiac arrhythmias, or life-threatening clinical complication. Neutropenia of any grade without fever will not be considered a contraindication to exercise training.

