#### 3.3.2. Feasibility and Adherence

The feasibility of the program will be measured by the rates of eligibility, recruitment, attrition, attendance (defined as: n _sessions attended_ × n _sessions prescribed_^−1^ × 100), and adherence to the program intensity and duration for each component of the intervention, i.e., aerobic, resistance and bone loading.

Attendance at the supervised sessions will be recorded by the supervising AEP, in addition to the self-reported completion of the weekly home-based session. Adherence records will be completed by the supervising AEP at each supervised session with detailed reasons for non-adherence recorded. Adherence to the aerobic component of the protocol will be defined as: minutes at the workload prescribed by the AEP, i.e., 12 min at moderate-to-vigorous intensity (60–85% HR_peak_) and 8 min at high intensity (>85% HR_peak_). Adherence to the resistance training component of the protocol will be defined as: minimum of 80 repetitions (5 exercises, 2 sets, 8 repetitions = 5 × 2 × 8) at a minimum intensity of 5/10 on the OMNI-RES scale [44]. Adherence to the bone loading component of the protocol will be defined as: minimum of 80 repetitions. The minimum intensity for adherence will be 2, where 1: isometric exercise targeting spine and/pelvis; 2: marching; 3: stomping; 4: jumping; 5: drop jump from height (range 10–30 cm). Unilateral exercises, i.e., marching, stomping, will have a minimum of 80 impacts per leg (4 × 20 impacts per leg), with a minimum of 80 total impacts for bilateral exercises, i.e., jumping, drop jumping from height.

*A**priori* cut points were defined to determine successful adherence to each component of the exercise program. Cut-off values for the feasibility criterion (a recruitment rate of ≥25% [106]; an attrition rate of <25% [107]; and attendance and adherence of ≥75% [108]) were established *a priori* as clinically relevant based on previous studies in other cancers.

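### Bone loading is planned to start at 40 impacts per session, but the minimum dose and the adherence criterion are both fixed at 80, so early sessions done exactly as planned count as non-adherent

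*Protocol article*

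**What the plan says.** Three statements in the protocol article bear on the bone-loading dose.

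- **Progression (section 2.5, Exercise Intervention):** "Bone loading activities will progressively increase across the intervention from 40 impacts per session to 100 impacts per session for non-affected skeletal sites".
- **Minimum (same paragraph):** "One minute rest periods will separate jump sets with a minimum of four sets of 20 impacts per set". Marching and stomping need 80 impacts per leg, and two-legged work is given "with a minimum of 80 total impacts for bilateral exercises, i.e., jumping, drop from height". No week, level or phase is attached to these minima.
- **Adherence (section 3.3.2, Feasibility and Adherence):** "Adherence to the bone loading component of the protocol will be defined as: minimum of 80 repetitions". The per-leg and total counts are repeated there, and an intensity floor is added: "The minimum intensity for adherence will be 2". Level 1 is isometric work and level 2 is marching.

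On recording, section 3.3.2 says "Adherence records will be completed by the supervising AEP at each supervised session". Among the feasibility criteria fixed in advance it lists "attendance and adherence of ≥75" per cent. Adherence is to be assessed separately for the aerobic, resistance and bone-loading components.

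Participants with pelvic, lumbar or lower-limb lesions are prescribed isometric exercise instead of the graded impacts.

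**The concern.** A planned dose that begins at 40 cannot also have a minimum of 80. The exercise physiologist has to choose. If the progression is followed, each session between 40 and 79 impacts breaks the stated minimum and fails the adherence criterion, although the participant did everything asked. If 80 is applied as soon as marching begins, the gradual build-up in impact volume from 40 is lost. Supervised sessions run at several sites, so different staff could resolve this differently.

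What is at stake is the meaning of the bone-loading adherence figure. Adherence is meant to show whether participants can do what the programme asks. As written, it can also fall because the programme asked for less than the scoring rule requires, and a reader of the result could not separate the two.

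**Working it through.** **Inputs.** From section 2.5: start 40, end 100, minimum four sets of 20. From section 3.3.2: threshold 80, intensity floor level 2, cut-off 75%. From the Abstract: 24 supervised sessions in the first 12 weeks. These are the base because adherence records are described for supervised sessions.

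**Step 1: the plan's own figure.** 4 × 20 = 80, which matches the stated minimum. The starting dose is 40/80 = 50% of it, or two sets of 20 instead of four.

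**Step 2: can the counting unit reconcile 40 with 80?**
- If 40 is per leg, it is below the 80 per leg required for marching and stomping.
- If 40 is a total, it is below the 80 in total required for jumping. The per-leg minimum would then mean 2 × 80 = 160 impacts over both legs, above the end dose of 100.
- If 80 were meant only once jumping starts, marching and stomping would still carry their own 80 per leg.
- If the low counts are level 1 work, section 2.5 sets no 80 minimum for level 1, but section 3.3.2 scores level 1 as non-adherent.

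No reading makes the early sessions adherent.

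**Step 3: how many sessions below 80 the cut-off allows.** Under pass/fail scoring, 24 × 0.25 = 6 sessions.

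**Step 4: score of a fully compliant participant.** The article gives neither the ramp nor the scoring rule, so both are assumptions here, and the sessions are taken to be at level 2 or above. Rule A is pass/fail at 80 for each session. Rule B is the mean of min(dose, 80)/80.

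For the linear ramp, the dose at session k is 40 + 60(k − 1)/23. It first reaches 80 at k = 17, which leaves sessions 17 to 24, i.e. 8 sessions.

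| Assumed ramp | Rule A | Rule B |
|---|---|---|
| Linear, 40 to 100 | 8/24 = 33% | 66.38/80 = 83% |
| 40/60/80/100, six sessions each | 12/24 = 50% | 65/80 = 81% |
| 40/80/100, eight sessions each | 16/24 = 67% | 66.67/80 = 83% |
| 40 for six sessions, then at least 80 | 18/24 = 75% | 70/80 = 88% |

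Rule B means: linear, (953.04 + 8 × 80)/24 = 66.38, where 953.04 = 16 × 40 + (60/23) × 120 is the sum of the first 16 doses; four steps, (6 × 40 + 6 × 60 + 12 × 80)/24 = 65; three steps, (8 × 40 + 16 × 80)/24 = 66.67; last row, (6 × 40 + 18 × 80)/24 = 70.

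The 75% cut-off is met in five of the eight cells: one under rule A and all four under rule B. In none does full compliance score 100%. Scored against the dose prescribed for each session, the same participant scores 100% in every row.

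**The case against.** **Fixed targets are the protocol's general approach.** All three components are scored against absolute thresholds. With five exercises, a permitted resistance prescription of two sets of six gives 5 × 2 × 6 = 60 repetitions, also below that component's threshold of 80. How often a target dose is reached is a legitimate feasibility measure. This stands as a reason not to insist on session-by-session scoring. It does not reconcile 40 with 80 inside one paragraph, and a target-dose measure should not be read as compliance during a planned ramp.

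**Level 1 could be the low-volume start.** Section 2.5 lists isometric work as the first intensity level and gives it no minimum of 80, so participants might begin there and move to 80 or more at level 2. The reading is strained, because isometric work produces no real impacts. At best it rescues delivery, since the level 2 floor still makes those sessions non-adherent.

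**Figure 2 or the full protocol may hold a schedule.** Neither is shown. A schedule could tell staff which figure governs, but the two sections as written would still disagree.

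**The aerobic criterion might look like a precedent for scoring against each session's prescription**, because it counts "minutes at the workload prescribed by the AEP". It is not one. The text goes on to fix 12 minutes at moderate-to-vigorous and 8 minutes at high intensity. It works because that target equals the prescription in section 2.5: 20 minutes including 2 × 4 = 8 at high intensity, leaving 12.

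**Conclusion.** The inconsistency is real and rests on explicit text. For participants without pelvic, lumbar or lower-limb lesions, planned sessions below 80 impacts or at level 1 are scored non-adherent when done as prescribed. Under pass/fail scoring this can take a fully compliant participant below the 75% cut-off (33% to 75% on the assumed ramps). Under capped proportional scoring the cut-off is met (81% to 88%), but the ceiling stays below 100%.

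Three stronger readings are not supported.

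- **That the trial will fail its bone-loading feasibility criterion.** This depends on a ramp and a scoring rule that the article does not give.
- **That the primary quality-of-life comparison or the sample size is compromised.** Neither uses this score. Section 5 mentions a 70% adherence cut-point when it describes the handling of missing data, but does not say which adherence measure that refers to, so no link to bone loading can be drawn.
- **That a low result for the whole component would be due to this conflict.** Participants with the listed lesions are prescribed level 1 work and miss the level 2 floor whatever the 40 and 80 say. That is a separate matter, and the share of such participants is not given.

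The point is worth correcting because the rule misclassifies compliant sessions and the correction is cheap. Its reach is a tertiary feasibility outcome and the delivery of the intervention.

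**What to change.** **Section 2.5.** Make the two figures agree: either start at 80, or apply the minimum of 80 only from a stated week or level. Say whether the range from 40 to 100 is per leg or in total. Which starting volume is right is a clinical decision.

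**Section 3.3.2.** Match the bone-loading criterion to the prescription, as the aerobic target already does, by one of two routes:
1. Apply the threshold of 80 only to sessions after the ramp has reached 80.
2. Score each session against the dose prescribed for it, and report the share of sessions reaching 80 as a separate figure.

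Under either route, say whether the 75% is a share of sessions or of dose. If Figure 2 or the full protocol already contains a week-by-week schedule, bring both sections into line with it.

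**Cost.** Rewording of two paragraphs. The second route also needs the prescribed dose as one extra field on the record kept at each supervised session. No extra visits or participants are needed.

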#### Stepped Down Supervision Approach

The modular multi-modal exercise program should be undertaken three times per week. For the first twelve weeks, two exercise sessions per week will be supervised by an AEP and once at home. For home-based sessions, elastic resistance bands will be provided, with advice for the purchase of dumbbells of appropriate weight. High intensity training will be replaced by a moderate intensity walk three times per week if a bike or treadmill is unavailable. Exercise supervision in the following three months will be stepped down to home-based sessions, with an optional weekly group class (2 to 6 participants) supervised by the study AEP. In addition, the AEP will telephone participants every two weeks to check on their adherence, any adverse events, prescribe progressions/regressions as appropriate, and answer any questions. Motivational interviewing will be used if any barriers are expressed. Following the first six months, all participants will be encouraged to maintain three exercise sessions per week for a further six months without group sessions. At the completion of their study involvement, participants will receive education regarding the Australian Government Department of Health Chronic Disease Management Plan, with no direct referrals to exercise physiologists or group classes.

## 3. Outcome Measures

The data and sample collection schedule is depicted in Figure 1, and detailed in Table 1. All testing sessions will be conducted in the research laboratories within the School of Human Movement and Nutrition Sciences at The University of Queensland and will be completed by two researchers, consistently assigned to the same tasks. Prior to each testing session, participants will be asked to: (i) maintain a hydrated state in the 24 h prior to testing; (ii) fast, including abstaining from caffeine and alcohol intake for 8 h prior to testing; and (iii) avoid any vigorous, high or unaccustomed moderate intensity physical activity for the preceding 24 h. Wherever possible, the testing session will be scheduled for the morning hours, with all subsequent testing timepoints scheduled at the same time of day for each participant. Prior to the baseline testing session, participants will be required to record a 3-day diet diary, which they will be required to replicate prior to all subsequent testing sessions. Participant adherence to the testing standardization measures will be evaluated prior to the commencement of each assessment. If testing standardization measures are not met, the researcher will confirm the participant’s understanding of the pre-testing requirements and reschedule the assessment for another day. Inter- and intra-tester reliability will be determined for data-collecting investigators for all outcome measures as appropriate. Assessments will be performed in a consistent order with appropriate rest periods to minimize testing fatigue. Any alterations in medical status or medications, hospital admission, or concomitant study participation will be documented for future reference during analysis of results.

### 3.1. Primary Outcome

#### Cancer-Specific Quality of Life (EORTC QLQ-C30 and QLQ-MY20)

The primary outcome of this study is HRQoL after the 3-month supervised exercise intervention compared with the waitlist control. HRQoL will be measured using the overall HRQoL summary score for the core HRQoL questionnaire of the European Organisation for Research and Treatment of Cancer Quality of Life Questionnaire (EORTC QLQ-C30, version 3.0) [46]. The EORTC QLQ-C30 is a widely used and well-validated cancer-specific instrument [3] with good psychometric properties in solid tumors [47,48]. It has acceptable reliability and validity in MM (Cronbach’s α = 0.70–0.92, except role function = 0.54), with an excellent ability to discriminate between patients in different objective disease states and a high responsiveness to changes in patients’ clinical status over time [3,49]. In a recent Delphi analysis, consensus was reached to collect patient-reported outcomes using the EORTC QLQ-C30 in patients with MM [50]. The minimal important difference (MID), defined as the smallest change in a HRQoL score considered important to patients that would lead the patient or clinician to consider a change in therapy, will be based on those estimated for individual scales of the QLQ-C30 in patients with MM [51].

The EORTC QLQ-C30 summary score encompasses all symptom (e.g., fatigue, pain) and function domains (e.g., emotional and social functioning) assessed by the QLQ-C30. The summary score is a strong prognostic factor for overall survival above and beyond that provided by clinical and sociodemographic variables for patients with MM [7]. The summary score also appears to have more prognostic value than the global QoL, physical functioning, or any other scale within the QLQ-C30 [7].

The European Organisation for Research and Treatment of Cancer Quality of Life Questionnaire Multiple Myeloma module (EORTC QLQ-MY20) is a reliable and valid instrument, recommended as a supplement to the QLQ-C30 instrument in patients with MM (Cronbach’s α = 0.70–0.92) [52]. As with the QLQ-C30, QLQ-MY20 domain scores are averaged and transformed linearly to a score ranging from 0–100. A high score for disease symptoms and side effects of treatment represents a high level of symptomatology or problems, whereas a high score for future perspective and body image represents better outcomes.

### 3.2. Secondary Outcomes

#### 3.2.1. Cardiorespiratory Fitness (V̇O_2peak_ and Oxygen Efficiency Uptake Slope)

A cardiopulmonary exercise test (CPET) will be conducted to determine V̇O_2peak_, which represents a strong predictor of decreased total cancer mortality risk independent of adiposity [53]. This measure has been found to be feasible and safe in a sample of patients with MM greater than six months post autologous stem cell transplantation and in remission [54]. The oxygen uptake efficiency slope (OUES), a submaximal index of cardiorespiratory reserve, will also be determined [55]. OUES has been shown to correlate with V̇O_2peak_ in older patients with colorectal cancer [56], indicating that it as a valid index for exercise tolerance. The exercise intensity (submaximal or maximal) does not affect OUES values [57]; hence, it is used in clinical conditions which prevent patients from being able to perform a maximal CPET. Additional parameters that will be determined from the CPET include test duration as a measure of exercise capacity and V̇O_2_ and power output at ventilatory threshold as measures of submaximal aerobic capacity.

V̇O_2peak_ testing will be conducted under medical supervision, with electrocardiography continually monitored throughout the protocol. All procedures will be carried out in accordance with the exercise testing criteria defined by the ACSM [40]. Prior to commencement, participants will be checked for any contraindications to exercise testing, including blood pressure measurement.

All V̇O_2peak_ testing will be completed using a cycle ergometer (Lode Rehcor, Lode B.V., Groningen, Netherlands). The V̇O_2peak_ test will require participants to progressively cycle to volitional fatigue; oxygen uptake (V̇O_2_) and carbon dioxide production (V̇CO_2_) will be measured continuously during exercise. Using a stationary metabolic cart system (COSMED Quark CPET, Rome, Italy), expired air will be analyzed for fractional expired oxygen (FEO_2_) and fractional expired carbon dioxide (FECO_2_) every 15 s during exercise from a mixing chamber, while minute ventilation will be recorded every 15 s using a turbine ventilometer. Gas analyzers will be calibrated immediately prior to testing and validated after each test using a certified beta gas mixture (BOC, Brisbane, Australia). The ventilometer will be calibrated before each test using a 3 L syringe (Hans Rudolph Inc., Shawnee, PA, USA) in accordance with the manufacturer’s instructions. V̇O_2peak_ will be recorded as the mean of the two highest consecutive 30 s V̇O_2_ readings, with a maximal test determined if the two highest readings demonstrate a plateau. The test will be determined to be invalid if it is terminated prior to reaching a ventilatory threshold. Peak power output will be recorded as the highest 30 s power output completed during the test.

The testing protocol, modified from Wasserman and Whipp [58], will begin with three minutes of rest for respiratory normalization, followed by four minutes of warm-up at no or very low resistance. Thereafter the electronic resistance provided by the cycle ergometer will increase incrementally by 10–15 watts each minute. To ensure the test lasts between 10 and 12 min, the researcher may use their clinical judgement to adjust the wattage for the warm-up and the test increments for participants with very low or very high predicted cardiorespiratory fitness. If adjustments to the warm-up wattage and increments are made, these will be replicated at all subsequent V̇O_2peak_ tests for that participant. Participants will be asked to maintain a cycling cadence between 60 and 70 revolutions per minute throughout the test.

Throughout the V̇O_2peak_ test, HR, blood pressure, and RPE (6–20 Borg scale) will be monitored. Blood pressure will be monitored every two minutes, whilst HR will be continuously monitored throughout the V̇O_2peak_ test using the COSMED automatic blood pressure cuff. Participants’ RPE will be recorded in the final 20 s of each minute. The test will be terminated when participants reach volitional fatigue, when participants choose to terminate exercise, or at the discretion of the researchers, in accordance with the indications for exercise test termination as outlined by the ACSM [40]. HR recovery will be monitored for 5 min immediately following the V̇O_2peak_ test, with participants only discharged from the laboratory once their blood pressure and HR return to within 10–15 mmHg and 15 bpm of pre-exercising levels.

